#### 2.2.3. Sampling Technique

Convenience sampling will be used to recruit healthy adults for this study. A purposive sampling method will also be used, where participants who underwent TKR will be identified through hospital records and invited to participate by the NHS trust research team. Participants who underwent TKR will be recruited from the Princess Elizabeth Orthopaedic Centre based at the Royal Devon and Exeter and the Nightingale Hospital Exeter. Convenience sampling and purposive sampling are appropriate because this research is exploratory in nature.

#### 2.2.4. Inclusion and Exclusion Criteria

Inclusion Criteria—Group of Participants who underwent TKR:Adults (aged 18 years and over);Individuals who have undergone total knee replacement in the past five to nine weeks.

Inclusion Criteria—Healthy Adult Group:Adults (aged 18 years and over);Participants with no previous musculoskeletal injuries (past six months) or current neuro-musculoskeletal disorders that affect standing and walking.

Exclusion Criteria:Individuals with cognitive impairment affecting their ability to participate and follow instructions safely;Individuals with any skin conditions or broken skin in the calf and behind the knee area;Individuals with deep brain stimulation or pacemaker implants or other implants that may interfere with the measurement system.

### 2.3. Home Testing

Participants recruited for the computer vision-based approach validation will then undertake the home testing procedure. The home testing protocol will take place in the participants’ own homes.

## 3. Materials and Methods

### 3.1. Focus Groups

Interviews will be conducted in a hybrid setting and recorded via Microsoft (MS) Teams (Microsoft, Washington, DC, USA). Interview transcripts will be coded using NVivo 15 software (Lumivero, Denver, CO, USA).

### 3.2. Validation of Computer Vision-Based Approach

#### 3.2.1. Physical Activity Assessment

Daily physical activity and sedentary time will be assessed using the Axivity AX3, a ‘wrist-worn’ tri-axial accelerometer (Open Lab, Newcastle University, Newcastle upon Tyne, UK). AX3 data will be downloaded using OMGUI software (open movement (V.1.0.0.37) and analysed using DigiPA software (version 4.01).

#### 3.2.2. Questionnaires

Questionnaire data will be collected using REDCap electronic data capture tools available at the University of Exeter. REDCap (Research Electronic Data Capture) is a secure, web-based software platform designed to support data capture for research studies [15,16]. Participants will be asked to complete the following seven questionnaires:A questionnaire on demographic data. This will include clinical scores and comorbidities (age, sex, ethnicity, handedness, smoking, marital status, drug history, and other medical conditions).The PROMIS-29 v2 (Patient-Reported Outcomes Measurement Information System). This measures both physical and mental health through a concise set of questions [17].The Oxford Knee Score (OKS). This is a validated measure used to assess pain and function in individuals who underwent total knee replacement or those who are suffering from knee arthritis [18].The Numeric Rating Scale (NRS). This is a pain assessment tool where individuals rate their pain on a numeric scale, typically ranging from 0 to 10, with 0 being no pain and 10 indicating the worst possible pain.The IPAQ Short Last 7 Days. This is the International Physical Activity Questionnaire used to assess physical activity in the past week. It measures moderate and vigorous activity along with walking in 10-min bouts within seven days [19].The Barthel Index for Activities of Daily Living (ADL). This measures functional independence, especially in patients who experienced a stroke or those with chronic disabilities. This ordinal scale focuses on personal care and mobility [20].The EQ-5D-5L. This is a health assessment tool that measures health status across five dimensions: mobility, self-care, usual activities, pain/discomfort, and anxiety/depression [21].

#### 3.2.3. Motion Capture

Each participant will be provided with a tight-fitting t-shirt and gym shorts. A full-body set of retroreflective markers (*n* = 60) based on the conventional gait model 2 [22] will be applied to the participant using surgical tape. Marker-based motion capture data will be collected using 12 Vicon Valkyrie VK16 cameras (Vicon, Oxford, UK). Data will be recorded at 100 Hz. Motion capture data will be processed in Vicon Nexus software (version 2.16) and analysed in Visual3D (C-Motion, Rockville, MD, USA).

Computer vision-based markerless motion capture will be run on two laptops to capture data: in the sagittal plane and at a 30° angle. Digimotion software (version 5.01) will be run locally on each laptop to activate the webcam and calculate hip, knee, and ankle angles in real time. Data will be recorded at 30 Hz. Two video cameras and three iPads/iPhones (Apple, Cupertino, CA, USA) will record videos from different angles to determine any angle effect. Digimove software (version 4.01) will calculate hip, knee and ankle angles from recorded videos. Videos will be recorded at 30 Hz.

#### 3.2.4. Surface Electromyography

Surface electromyography (sEMG) data will be recorded using Trigno Avanti Sensors (2148 Hz, Trigno Wireless System, Delsys, Sale, UK). Twelve sEMG electrodes will be placed bilaterally to avoid the general location of innervation zones and distal tendon areas [23] over the following muscles: vastus lateralis, vastus medialis, semitendinosus, biceps femoris, tibialis anterior, and the medial head of the gastrocnemius.

### 3.3. Home Testing

Participants will use their own mobile phones or tablet devices to record a video of themselves completing the movement tasks. Participants will upload their videos to REDCap [15,16].

## 4. Procedure Details

### 4.1. Focus Groups

Focus groups will be conducted in a hybrid environment, where participants can attend in person or via MS Teams. Initially, separate focus group sessions will be conducted with staff and service user groups. Printed question sheets will guide group discussion. Each group will have a researcher facilitating the discussion. Following the separate focus group sessions, groups will be mixed to enable a more diverse discussion perspective. Each focus group session will last 75–90 min.

#### Thematic Analysis

A thematic content analysis of the interview transcripts will be used to investigate the usability and perceived usefulness of the computer vision-based approach (by clinicians and people who underwent TKR). It will also be used to explore participants’ experiences of symptoms.

Focus group transcripts will be transcribed verbatim. Two reviewers will independently code each interview, and any discrepancies identified after the initial four transcripts will be resolved. An interim analysis of the first 15 participants will determine if thematic saturation has been achieved.

To explore usability factors, the transcripts will undergo a thematic analysis. Personal documentation will be initially reviewed through a content analysis, with a more detailed thematic approach applied if needed. Data inconsistencies will guide a member-checking process with participants, conducted before the write-up and dissemination of findings.

### 4.2. Validation of Computer Vision-Based Approach

Participants will wear an activity monitoring accelerometer for one week before the experimental session at the university. The accelerometer will be removed at the session. Physical activity monitoring can be repeated in the week following the visit if there are any problems with the data.

Motion capture markers and sEMG electrodes will then be applied. A physiotherapist will administer questionnaires.

A static trial will be recorded, followed by a series of gait/functional tasks. Participants will complete a two-minute walk on a treadmill at a self-selected walking speed. A sit-to-stand test will then be completed three times: participants will start in a seated position and stand up, then sit down without the use of their hands.

Participants will then be asked to complete the timed-up-and-go test (TUG) three times. The participant will start by sitting down in a chair and will stand up, walk forward three metres, turn around a cone, and then walk back to the chair before sitting down. Finally, an overground walking task will be completed three times: the participant will be asked to walk five metres, turn around a cone, and walk another five metres.

Knee range of motion will be measured by a trained physiotherapist. The maximum and minimum angles will be measured using a universal goniometer whilst lying on a physiotherapy couch and whilst seated on a chair.

Participants will be offered the chance to rest between procedures for as long as preferred. The Single Ease Question (SEQ) is a concise post-task questionnaire utilising a seven-point rating scale to gauge the perception of the difficulty or ease of a specific task. The SEQ will be completed after every task. Following the completion of testing, all equipment will be removed from the participant.

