Functional tasks that reflect daily movements, such as the sit-to-stand task, could be used to monitor knee ROM. These tasks are easier to complete in the home environment than goniometer measurements and represent functional ability. The sit-to-stand test is recommended for monitoring recovery from TKR surgery [10]. Evidence suggests that sagittal plane knee ROM is decreased during the sit-to-stand task after TKR surgery compared to healthy controls [11], indicating that this task may be used to measure ROM in post-operative patients. Therefore, this study will use the sit-to-stand test to measure ROM in a home-based setting.

The computer vision-based approach offers a non-invasive, objective method to monitor knee flexion in patients with knee stiffness, which could inform treatment decisions to improve outcomes. Currently, no tool exists to remotely and accurately detect early post-surgical knee stiffness. This study seeks to develop a cost-effective tool for measuring and quantifying knee stiffness pre- and post-TKR surgery for use across the NHS. This study also aims to determine its reliability, feasibility, and usability for implementation in the home.

The primary objectives of the study are the following:To provide proof of concept for a computer vision-based approach that measures knee ROM for use in the home setting.To validate the computer vision-based approach in people who have undergone TKR by ascertaining the test–retest reliability of algorithm outputs such as knee flexion/extension angles.To investigate the integration of the computer vision-based approach into clinical practice through focus groups and identify key development areas for successful implementation.

The secondary objectives of the study are the following:To explore how pain influences knee ROM in people who undergone TKR.To investigate the relationship between muscle activation and ROM in people who have undergone TKR and in healthy controls.To describe the association between physical activity and ROM in people who have undergone TKR.To identify the potential risk factors, measured using questionnaires, linked with knee stiffness post-TKR surgery.

This study will be split into three stages: (1) focus groups, (2) validation of the computer vision-based approach for measuring knee range of motion in the laboratory, and (3) home testing. These will be outlined and addressed separately within the protocol.

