#### Data Analysis 

Descriptive and frequency statistics will be reported for demographic, usability, acceptability, and feasibility data, and missing data will be reported.

To validate the motion capture measurements of the computer vision-based motion capture software against those from the marker-based motion capture software, we will use Bland–Altman (Tukey mean-difference) plots to assess for systematic deviation and determine any necessary bias correction.

To determine the test–retest reliability of the motion capture knee ROM measurements and to identify potential risk factors associated with knee stiffness, we will apply mixed-effects linear models for knee ROM adjusted for the group (group that underwent TKR or control) and questionnaire scores, with random effects for each participant. Variance components of the mixed-effects model may be used to estimate reliability measures as follows:

Relative reliability will be estimated using the intra-class correlation (2) (ICC) of Two-Way Random Effects [24]. Interpretation of ICC values will be conducted according to published guidance: an ICC of less than 0.5 is considered poor, between 0.5 and 0.75 is moderate, between 0.75 and 0.90 is good, and above 0.90 is excellent [25]. Absolute reliability will be estimated by the standard error of measurement (SEM) [26], calculated as $SD\left(standard\;deviation\right)\times \surd (1-ICC)$. The Minimal Detectable Change at the 95% confidence level (${MDC}_{95}$) is the minimal amount of change that would be accepted as a real change greater than that seen due to random variation or error [26]. MDC_95_ is calculated as follows: ${MDC}_{95}=1.96\times SEM\times \sqrt{2}$.

To explore the relationship between knee ROM and pain, muscle activation, physical activity, and potential risk factors, appropriate correlations/statistical tests will be selected to describe associations.

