### 4.3. Home Testing

Participants will be asked to set up a camera device (mobile phone/tablet) in their homes and record themselves completing the following:The sit-to-stand test;If possible (within the limitations of the participants’ available space and ability to capture the trial), the TUG walk.

The research team will send the participants an email that will allow them to upload their video files to REDCAP. Videos will be analysed using a custom computer vision-based application. Participants will be asked to complete a System Usability Scale questionnaire [27,28]. The participants will be asked to complete this task within a week of the lab visit.

Descriptive and frequency statistics will be reported for the System Usability Scale questionnaire, and missing data will be reported. Knee ROM will be compared to the $MDC_{95}$ to determine compatibility with lab-based measurements.

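### The planned test–retest reliability is within-session repeatability, so its MDC95 is too small a yardstick for recordings made on another day with another set-up

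*Protocol article*

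**What the plan says.** Section 1 (Introduction) of the Protocol article lists as a primary objective the validation of the approach in people with total knee replacement by "ascertaining the test–retest reliability of algorithm outputs such as knee flexion/extension angles". The Data Analysis part of section 4.2 takes this up: "To determine the test–retest reliability of the motion capture knee ROM measurements", a mixed-effects linear model is fitted "with random effects for each participant". Then: "Relative reliability will be estimated using the intra-class correlation (2) (ICC) of Two-Way Random Effects". The second factor of that two-way model is not named. SEM is SD × √(1−ICC), and MDC95 is 1.96 × SEM × √2. The MDC95 is described as the smallest change to be accepted as real rather than as random variation or error.

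The lab procedure in section 4.2 is a single visit. The accelerometer is worn for a week "before the experimental session at the university", markers and electrodes are then applied, and the tasks follow: "A sit-to-stand test will then be completed three times". The timed-up-and-go and overground walking tasks are also done three times. Then: "Following the completion of testing, all equipment will be removed from the participant". No second lab visit and no renewed camera set-up is described.

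The only other occasion is the home recording in section 4.3, made with the participant's own phone or tablet: "The participants will be asked to complete this task within a week of the lab visit". It is not described as an input to the reliability estimate. Home knee ROM is compared with the MDC95 to decide whether it is compatible with the lab measurement.

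**The concern.** Test–retest reliability asks whether a second measurement, made on a separate occasion with the equipment set up afresh, gives the same answer. Repeats within one visit cannot show this. Whatever is particular to that day and that camera placement is shared by all of a participant's trials, so the model assigns it to the participant. It is then counted as true difference between people, which raises the ICC and lowers the SEM and MDC95.

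The MDC95 is nevertheless defined as covering random variation or error in general, and its one stated use is across a change of day, device, setting and camera placement. The errors left out of the threshold are those present where it is applied. At stake are the meaning of a primary result and the conclusion on whether home recordings agree with the lab.

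**Working it through.** **Inputs.** From the article: one session, three trials per task, participant as the only named random effect, and the SEM and MDC95 formulas (all section 4.2); home recording within a week on the participant's own device (section 4.3). The article states no value for any SD, ICC, SEM or MDC95, so there is no planned figure to reproduce on this point. All values in degrees below are assumptions.

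**What the planned MDC95 contains.** Let σb be the between-person SD, σo the set-up/occasion SD and σw the trial SD.

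- Single-session ICC = (σb² + σo²) / (σb² + σo² + σw²), because σo cannot be separated from σb with one occasion.
- SEM = SD × √(1−ICC) = √(σb² + σo² + σw²) × √(σw² / (σb² + σo² + σw²)) = σw.
- Planned MDC95 = 1.96 × √2 × σw = 2.77 σw, whatever σo is.
- Between-occasion MDC95 = 2.77 × √(σw² + σo²).
- Ratio of the two = √(1 + σo²/σw²). It equals 1 only if σo = 0, and is 1.41 if σo = σw.

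**Consequence for unchanged participants.** A difference between single trials on two occasions has SD √(2(σw² + σo²)). With no true change and no home–lab bias, the share beyond the planned MDC95 is 2Φ(−1.96 / √(1 + σo²/σw²)).

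| σw | Planned MDC95 | σo | Between-occasion MDC95 | Share beyond planned MDC95 |
|---|---|---|---|---|
| 1° | 2.8° | 1.5 / 2 / 3° | 5.0 / 6.2 / 8.8° | 28 / 38 / 54% |
| 2° | 5.5° | 1.5 / 2 / 3° | 6.9 / 7.8 / 10.0° | 12 / 17 / 28% |
| 4° | 11.1° | 1.5 / 2 / 3° | 11.8 / 12.4 / 13.9° | 7 / 8 / 12% |

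The nominal share is 5%. One cell in full, for σw = 2° and σo = 3°: √(1 + 9/4) = 1.80; 1.96/1.80 = 1.09; 2Φ(−1.09) = 0.28.

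**Simulation check.** This used 60 participants, three trials in one session, σw = 2°, σb = 10° and 2,000 runs. The mean single-session MDC95 stayed at 5.5° for σo of 0, 1, 2, 3 and 4°. The share beyond it was 5, 8, 17, 28 and 39%. The single-session ICC stayed at 0.96 to 0.97, while the between-session ICC was 0.96, 0.95, 0.93, 0.89 and 0.83. On the article's own scale, the last two drop from excellent to good.

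**Averaging.** The article does not say whether single trials or means of three are compared. Take σw = 2° and σo of 1.5, 2 or 3°. If three-trial means are used throughout, the MDC95 is 5.54/√3 = 3.2° and the shares are 23, 33 and 48%. If a single-trial MDC95 is applied to three-trial means at both places, they are 4, 9 and 22%.

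**The case against.** **Which repeats feed the ICC is not stated.** This stands. The second factor is unnamed, and variance components are only said to be possibly used. Section 3.2.3 plans two laptop views, two video cameras and three iPads or iPhones to look for an angle effect. If view were the second factor, some view-related error would enter, so it would be too strong to say that the MDC95 holds nothing but trial noise. But these views film the same movement on the same day and are not linked to the ICC or MDC95. They cannot supply the error from setting up again or from another day.

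**The size is assumed.** This also stands. Only the direction follows from the design; as the table shows, the size depends heavily on the ratio of σo to σw.

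**The stated use makes the test stricter, not laxer.** True. In section 4.3 a small MDC95 counts against the home method rather than hiding its error. It is still a wrong yardstick, because ordinary occasion error would be read as incompatibility.

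**Two stronger readings are not supported.** A reader might infer that the objective will be declared met on an inflated ICC, but the article sets no ICC pass mark, only descriptive bands. A reader might also infer that this MDC95 is the fixed threshold for remote monitoring. Section 5 speaks only of possible personalised thresholds in later work.

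**It is a pilot, and an analysis plan may settle the rest.** Pilot status bears on sample size, not on what a reliability estimate measures. An analysis plan can name the ICC factor, but it cannot create a second comparable lab session.

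**Conclusion.** The point holds. As described, the design yields within-session repeatability, possibly with some view error, under the name of test–retest reliability. Its MDC95 is too small for comparisons across occasions by the factor √(1 + σo²/σw²), for any non-zero set-up or day-to-day variance. With single-trial comparisons, no true change, no home–lab bias, σw of 1 to 4° and σo of 1.5 to 3°, between about 7% and 54% of unchanged participants would exceed it, against a nominal 5%. These figures are illustrations, not estimates.

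In the one use that the article fixes, the effect is to mark home recordings wrongly as incompatible with the lab. Reading noise as real loss or gain of motion would follow only if the same MDC95 were later adopted for monitoring. That the three trials feed the ICC is an inference, though the described procedure offers no other lab repeats of one task by one method except further movement within the same session.

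**What to change.** 1. Report the three-trial ICC, SEM and MDC95 as within-session repeatability, reword the objective and the Data Analysis text to match, and name the second ICC factor. Do not present this MDC95 as the threshold for real change between days.
2. In section 4.3, replace the comparison with the MDC95 by lab–home bias and 95% limits of agreement for sit-to-stand ROM, from the recordings already planned, separately for patients and controls. State that day, device, setting and set-up change together, so the result is total home–lab disagreement and not a pure occasion component. Do not derive an MDC95 from these differences and then use it to test lab–home compatibility, because that would be circular.
3. Optionally, record one further sit-to-stand set at the same visit with the camera taken down and placed again. This estimates set-up error only, not day-to-day error, and it cannot be added once a participant's visit is over.

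The cost of (1) and (2) is wording and a different summary of data already being collected; (3) adds a few minutes per visit. The downside is a less favourable reliability claim.

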#### Data Analysis 

Descriptive and frequency statistics will be reported for demographic, usability, acceptability, and feasibility data, and missing data will be reported.

To validate the motion capture measurements of the computer vision-based motion capture software against those from the marker-based motion capture software, we will use Bland–Altman (Tukey mean-difference) plots to assess for systematic deviation and determine any necessary bias correction.

To determine the test–retest reliability of the motion capture knee ROM measurements and to identify potential risk factors associated with knee stiffness, we will apply mixed-effects linear models for knee ROM adjusted for the group (group that underwent TKR or control) and questionnaire scores, with random effects for each participant. Variance components of the mixed-effects model may be used to estimate reliability measures as follows:

Relative reliability will be estimated using the intra-class correlation (2) (ICC) of Two-Way Random Effects [24]. Interpretation of ICC values will be conducted according to published guidance: an ICC of less than 0.5 is considered poor, between 0.5 and 0.75 is moderate, between 0.75 and 0.90 is good, and above 0.90 is excellent [25]. Absolute reliability will be estimated by the standard error of measurement (SEM) [26], calculated as $SD\left(standard\;deviation\right)\times \surd (1-ICC)$. The Minimal Detectable Change at the 95% confidence level (${MDC}_{95}$) is the minimal amount of change that would be accepted as a real change greater than that seen due to random variation or error [26]. MDC_95_ is calculated as follows: ${MDC}_{95}=1.96\times SEM\times \sqrt{2}$.

To explore the relationship between knee ROM and pain, muscle activation, physical activity, and potential risk factors, appropriate correlations/statistical tests will be selected to describe associations.

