#### 2.2.2. Sample Size

Sixty participants (thirty participants who underwent total knee surgery five to nine weeks prior and thirty healthy controls) will be recruited for the project. Formal sample size estimates are not required for pilot and feasibility studies (PAFs). The choice of sample size (60 participants, 40 with complete data) reflects a balance between a large enough sample to represent population diversity and provide estimates of variability while ensuring that recruitment is achievable (participant drop-out and approximately 50% of eligible participants recruited). While there are no specific recommendations for sample sizes for PAFS, a general rule of thumb suggests a minimum of 30 people [13]. Twenty to thirty people are generally sufficient to estimate the standard deviation of outcome measures to estimate the sample size for a definitive clinical trial based on known estimates of Minimal Clinically Important Differences [14].

For the chosen sample size of 30 participants in each group, the power to detect varying effect sizes at a statistical significance level of 5% is shown in Table 1.

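### The post-TKR risk-factor objective is assigned to a model pooling patients with healthy controls, so its score coefficients need not equal the TKR slopes

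*Protocol article*

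**What the plan says.** The last secondary objective in the Introduction is confined to patients: "To identify the potential risk factors, measured using questionnaires, linked with knee stiffness post-TKR surgery". The muscle-activation objective in the same list names patients and healthy controls together, so the populations differ by objective.

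The Data Analysis part of Section 4.2 gives one model family two jobs, test–retest reliability and risk factors: "to identify potential risk factors associated with knee stiffness, we will apply mixed-effects linear models for knee ROM adjusted for the group". The covariates follow: "group that underwent TKR or control) and questionnaire scores, with random effects for each participant". No group-by-score term and no TKR-only fit is stated. A later sentence adds a second route: "To explore the relationship between knee ROM and pain, muscle activation, physical activity, and potential risk factors, appropriate correlations/statistical tests will be selected". It names neither the method nor the population.

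On the sample, Section 2.2.2 says "Sixty participants (thirty participants who underwent total knee surgery five to nine weeks prior and thirty healthy controls) will be recruited", and expects "60 participants, 40 with complete data". On controls, Section 2.2.3 says "Convenience sampling will be used to recruit healthy adults for this study". Patients qualify as "Individuals who have undergone total knee replacement in the past five to nine weeks" (Section 2.2.4). Age and sex are collected in the demographic questionnaire, one of the seven listed in Section 3.2.2. Time since surgery is not named there or in the model.

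**The concern.** With group as a main effect only, the model forces one slope per score on both groups. Controls have no replaced knee, so their slope is not part of the question, yet it contributes to every coefficient. A score related to ROM in patients but not in controls would be reported as a weaker association than patients show, and could be passed over.

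Two covariate questions add to this. Patients are measured at different times within a five-to-nine-week window. If both ROM and a score such as pain or function move with recovery, part of the score coefficient may reflect weeks since surgery. That variable is undefined for controls, so it cannot simply be added to the pooled model. The wording also leaves open whether age and sex are adjusted for.

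**Working it through.** **The plan's own figure.** Table 1 gives power at 30 per group and a 5% level. A two-sided two-sample t-test gives 0.119, 0.208, 0.332, 0.478, 0.628, 0.760, 0.861, 0.929 and 0.968 for effect sizes 0.2 to 1.0. Every cell of the table is reproduced. The table therefore describes a difference in means between the groups and says nothing about the precision of score slopes.

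**What the pooled coefficient estimates.** Take one score, a group main effect, no interaction, and equal numbers of repeats per participant. Then

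pooled slope = w × (TKR slope) + (1 − w) × (control slope),

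w = n_T s_T² / (n_T s_T² + n_C s_C²),

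where s is the within-group SD of the score. With n_T = n_C = 30 (Section 2.2.2) this becomes w = 1/(1 + r²), with r = s_C/s_T. The documents give no score SDs, so r is an assumed range:

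| r | w |
|---|---|
| 1 | 1/2 = 0.50 |
| 0.5 | 1/1.25 = 0.80 |
| 0.25 | 1/1.0625 = 0.94 |

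If the control slope is zero, w is the fraction of the TKR slope that the model returns. If the two slopes are equal, nothing is lost.

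**Check by simulation, with age.** All inputs are assumptions: 30 per group, TKR slope 5° per TKR SD of the score, control slope 0, residual SD 8°, age effect −0.2° per year, age–score correlation 0.3, mean age 70 (SD 8) in TKR and 40 (SD 15) in controls, 3,000 runs. Mean estimated slopes:

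| Model | r = 1 | r = 0.5 | r = 0.25 |
|---|---|---|---|
| Pooled, no age | 1.84 | 3.20 | 4.00 |
| Pooled, with age | 2.63 | 4.07 | 4.73 |
| Pooled, no age, age-matched controls | 2.06 | 3.45 | 4.08 |
| TKR only, no age | 4.57 | 4.49 | 4.50 |
| TKR only, with age | 5.07 | 4.97 | 4.98 |

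Pooling is the main source of error at r = 1 and r = 0.5. At r = 0.25 the age adjustment matters more. Matching the controls on age changes little.

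**What a TKR-only analysis can detect.** By Fisher's z, at 80% power and two-sided 5%, the detectable correlation is tanh[(1.960 + 0.842)/√(n − 3)]:

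- n = 60 pooled: 0.355
- n = 30 TKR: 0.492
- n = 20 TKR: 0.591

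The figure of 20 assumes that the 40 complete participants split evenly (40/2); the article does not give the split. Adjusting for three covariates replaces n − 3 by n − 6, which gives about 0.52 (n = 30) and 0.63 (n = 20).

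**The case against.** The strongest reply is that the dilution may be small where it matters most. Healthy adults should sit near the ceiling or floor of a knee-specific score. If the SD were 8 in patients and 2 in controls (assumed), the TKR weight would be 64/(64 + 4) = 0.94, a loss of about 6%. That stands. It does not extend to scores that vary as much in controls as in patients, as general health or activity scores might.

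Second, the later sentence on correlations and tests offers another route to the same objective. It does, but with no method or population fixed it does not correct the model that is stated.

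Third, this is the last secondary objective of a small exploratory study that openly discusses selection bias, and a fuller plan may hold the covariate list. That limits the weight of the point. The stated mismatch between objective and model remains.

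A reader might also infer several stronger criticisms that the text does not support:

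- *Age and sex are omitted.* They sit in one of the seven questionnaires, so the wording is ambiguous rather than a clear omission.
- *All scores enter together, on too few patients.* The article speaks of models in the plural and does not state simultaneous entry.
- *Unmatched controls spoil the score slopes.* The group term absorbs the mean age difference. A mismatch mainly affects the group coefficient, and the simulation shows little gain from matching.
- *Collinearity of knee scores with group is a reason to drop controls.* With group in the model, the slope already rests on within-group spread. In the example above, a TKR-only fit has 64 units of it against 68 pooled, so dropping controls recovers no precision.
- *Concurrent measures are presented as causes.* The article calls the factors potential and speaks of describing associations.

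**Conclusion.** The point holds in a limited form. The objective concerns patients after TKR, while the stated model pools them with controls under a single slope per score. The coefficient need not equal the TKR slope. If the association is absent in controls, it is 50% to 94% of that slope for control SDs from equal to a quarter of the TKR SD. That range rests on assumed SDs and a zero control slope. It would go too far to say that the model cannot answer the TKR question, because the bias vanishes if slopes are equal and is small if controls have little spread. Time since surgery is not named in the model, and the status of age and sex is unclear. The change is worth making because it is cheap, but nothing in the primary objectives depends on it.

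**What to change.** In the Data Analysis part of Section 4.2, separate the two purposes. Keep the pooled mixed model for reliability. For risk factors, state that associations with knee ROM are estimated in TKR patients only, one score at a time, adjusted for weeks since surgery, age and sex. Report them with 95% CIs and describe them as cross-sectional associations. An equivalent option is to keep both groups, add group-by-score terms and report the TKR slope, with weeks since surgery entered for patients only (centred, and set to zero for controls). Name the same population in the sentence on correlations and tests.

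The cost is wording. Age and sex are collected, and time since surgery must be known to establish eligibility. The downside is wider intervals, as the detectable correlations above show, so only large associations could be picked out. Age-matching the controls would be a recruitment change and is not needed for this objective.
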